### DI arm

The overall content of the intervention consists of an individualized diet modification proposal that will promote an energy deficit. The educational components of healthy eating habits will be based on national and international recommendations [4, 35]. Strategies and approaches to be applied include self-monitoring of food intake; realistic goal-setting, using behavior-specific goals and a step-wise approach to promote self-efficacy; addressing body image concerns and prevention of cancer relapse.

Safe weight loss should be achieved through a balanced diet according to the Italian dietary reference intakes [36]. Key strategies will emphasize the reduction of energy density by low-energy dense foods (e.g., water- and fiber-rich vegetables and fruits), limiting the intake of foods and beverages high in fat and added sugar, and limiting portion sizes.

Each goal will be stated and verified at each contact (reduce the portion size of cheese instead of normal portion size; choose fresh fish, instead of preserved fish, freshly squeezed lemon juice in water, instead of soft drinks). Participants will also be advised not to fall too far below their goal to support nutritional adequacy.

### PAI arm

The PAI will be designed on an individualized level, whereby specific activities are planned based on capabilities, lifestyle pattern and preferences so as to increase physical activity and to reduce sedentary time. Realistic and achievable goals will be set working toward short-term and long-term goals. A priority will be placed on regular planned aerobic exercise, since this creates an energy deficit that is much greater per unit of time than strength training. The general exercise prescription planned will be of low to moderate intensity, regular frequency, involving aerobic, resistance or mixed exercise types. The physical activity targets are: to be moderately physically active, equivalent to brisk walking for at least 30 min a day (short-term goal); to do purposeful exercise at a moderate level of intensity at least 60 min/day or ≥30 min of vigorous physical activity every day (long-term goal) [34, 37]. Reasonably, the initial goal will be to plan and implement daily purposeful mild to moderate exercise for a minimum of at least 10 min/day with a stepwise increase in time and intensity that will be evaluated and modified at each contact. Women who exercised at a higher level than 10 min/day at baseline will be instructed to aim for an incrementally greater goal of daily exercise and to plan to increase intensity as tolerated. Participants will wear the wrist-based activity monitor and they will be instructed to count the total number of steps to improve their self-monitoring and to reduce sedentary time.

Personalized goals will be set to increase physical activity. Each goal will be stated and verified at each contact (use public transportation to go to work instead of the car; use the stairs instead of using the elevator, check the wrist-based activity monitor). Safe increased physical activity should be recommended through a program tailored to individual characteristics. Participants will be instructed to report any problem or adverse event immediately to the clinical staff.

### PADI arm

The intervention will be focused on weight loss combining a reduced energy intake, an increase of physical activity, and reduction of physical inactivity. Women randomized to this arm will be offered an integrated version of both intervention components of the DI and PAI arms. This integrated approach will be weighted to avoid intervention overload. Individualized goals will be set for all participants to promote individualized diet modification and individualized physical activity based on individual characteristics.

### LII arm

Participants included in the LII arm will be considered as the control group. They will receive general counseling on health to reduce weight, and be provided with materials and guidelines available to the general public [4, 34, 35] and receive two motivational phone calls.

### Measures

Weight, and waist and hip circumferences will be measured at baseline, at 6-, 12-, and 24-month follow-up visits. Height will be measured at baseline. A fasting blood sample will be collected at baseline, at 6, and 24 months to measure lipid profile (total, HDL, LDL and VLDL cholesterol and triglycerides) and estradiol, insulin, glucose, and C-reactive protein level (Table 1).

Body composition will be assessed at baseline and at 6-, 12- and 24-month follow-up visits, using bioelectrical impedance vector analysis (BIVA) (Nutrilab device, AKERN Srl, Pontassieve, Italy). BIVA is a more accurate method for a quick measurement of body compartments [38, 39]. The direct analysis of the two components of the impedance vector (Z), resistance (R, Ohm), and reactance (Xc, Ohm), allows a semiquantitative evaluation of body composition in terms of body cell mass and hydration status. Data for total body water (TBW), body cell mass (BCM), extracellular water (ECW), fat-free mass (FFM), fat mass (FM) and percentage fat mass (% FM) will be available for all participants and will be used for identifying changes of fat and fat-free mass over the study period.

Physical activity will be also measured via the International Physical Activity Questionnaire (IPAQ) at baseline, 6 and 24 months. This questionnaire consists of questions that record the frequency and duration of mild, moderate, and strenuous exercise performed during free time in the previous 7 days measuring physical activity and inactivity. It is a validated self-report measure of exercise that has been reliably used in previous studies [40]. The total hours per week spent in each activity will be multiplied by the estimated metabolic cost of each activity [metabolic equivalent (MET) value] as determined from the Compendium of Physical Activities [41].

Dietary intake will be measured at baseline, 6 and 24 months using the validated and self-administered food frequency questionnaire (FFQ) developed for the European Prospective Investigation into Cancer and Nutrition Italian section (EPIC) study [42, 43]. It records daily intake of foods and nutrients over the previous year. It consists of 15 sections (first course, second course, side dish, fruit, etc.) and contains 254 questions investigating a wide range of food items.

Quality of life (QoL), health status and anxiety will be measured at baseline, 6-, 12- and 24-month visits using the Functional Assessment of Cancer Therapy-Breast (FACT-B) and State-Trait Anxiety Inventory (STAI) questionnaires. The FACT-B is a 37-item validated multidimensional self-report questionnaire, subdivided into four primary QoL domains and a disease-specific domain – additional concerns for breast cancer [44]. The subscales measure physical, social, emotional, and functional well-being, relationship with the doctor, and breast cancer concerns. The FACT-B has a 5-point Likert-type response scale. It has good psychometric properties, discriminates well between clinically distinct groups, and is responsive to change.

The STAI is a psychological inventory based two 20-item self-report measures. It assesses how respondents feel “right now, at this moment” and how respondents “generally feel”. In addition, the STAI State and Trait each have been found to contain two factors, which Spielberger labeled anxiety-present and anxiety-absent [45]. Respondents are asked to rate themselves on each item on the basis of a 4-point Likert scale, ranging from “not at all” to “very much so” for the STAI State and from “almost never” to “almost always” for the STAI Trait.

The intervention will propose the use of a pedometer-like device (a wristband) that encourages both increased physical activity and decreased sedentary time. This device is able to record total steps taken, total distance traveled, total time active during the day, and the greatest length of time of consistent movements done during the day. In addition it records light and deep sleeping time. All participants will receive and will have to wear the wrist-based activity monitor during the 6-month study period (days and nights). They could use a smartphone or a computer application to obtain feedback on their activity and sedentary time.

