## Methods/design

### Study design

The present study (InForma) was designed as a mono-institutional randomized controlled four-arm parallel-group trial. Randomized patients will receive a 6-month intervention and will be followed for further 18 months (Fig. 1).

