### Intervention

The principal aim of the intervention is to promote weight loss through diet and physical activity alone or in combination. The target goal is a 5 % weight loss 6 months after randomization. Participants will be followed up for a further 18 months and secondary outcome assessments will be made at 12 and 24 months (Table 1).

**Table 1 Tab1:** Study assessments

Assessments	Instrument	Visits			
		Baseline	6-month	12-month	24-month
Total, HDL, LDL and VLDL cholesterol, triglycerides, estradiol, insulin, glucose and C-reactive protein	Blood test	√	√		√
Height^a^, weight, waist and hip circumference, body mass index, waist-to-hip ratio	Calibrated scales, stadiometer, tape measure	√	√	√	√
Body composition (including total body water (TBW), body cell mass (BCM), extracellular water (ECW), fat-free mass (FFM), fat mass (FM) and percentage fat mass (% FM)	Bioelectrical impedance vector analysis (BIVA) (Nutrilab device, AKERN Srl – Italy)	√	√	√	√
Dietary target	24 hr recalls and/or food diary	√^b^	√		
Steps	Pedometer-like device	√^b^	√		
Diet	Food Frequency Questionnaire (FFQ)	√	√		√
Quality of life	Functional Assessment of Cancer Therapy- Breast (FACT-B)	√	√		√
Mood	State-Trait Anxiety Inventory (STAI)	√	√		√
Physical activity	International Physical Activity Questionnaire (IPAQ)	√	√		√

^a^Height will be assessed only at baseline

^b^24 hr recalls and/or food diary and the pedometer-like device will be used during the intervention to monitor individualized goals

Baseline assessment will be made for all participating women, prior to randomization in one of the four intervention arms (DI, PAI, PADI, and LII). All participants must wear the wrist-based activity monitor during the 6-month intervention period (day and night).

Participants randomized to one of the three intervention arms (DI, PAI, and PADI) will be given individualized counseling based on their lifestyle habits to reduce their weight. The motivational interviewing approach will be used to discuss behavior change that fosters a constructive specialist-patient relationship which could lead to better body weight control for the patients.

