The intervention will begin with an intensive phase consisting of monthly contacts: three face-to-face meetings, one group meeting and two motivational phone calls. The group sessions are planned for closed groups of an average of ten women per arm and will consist of a motivation and information session to discuss strategies and to reinforce guidance. The participants may invite a caregiver or a relative during the group meeting. The meeting aims to offer a caring and supportive environment where its members support each other and explore new strategies to create long-lasting positive changes. At baseline, their requirement for weight maintenance will be calculated using the Schofield equation [32] and then multiplied by their current physical activity level before applying a caloric restriction of about 500–1000 kilocalorie (kcal)/day [33, 34].

Individualized goals will be set for all participants included in the three intervention arms to promote weight loss. These goals will be verified at each contact and workable solutions will be proposed in case of specific problems. The contents of all contacts are presented in Table 2.

**Table 2 Tab2:** Delivery and contents of the 6-month intervention visits for participants randomized to the intervention arms: Dietary Intervention (DI); Physical Activity Intervention (PAI); Physical Activity; and Dietary Intervention (PADI)

	Contact 1	Contact 2	Contact 3	Contact 4	Contact 5	Contact 6
Contact	Face-to-face	Telephone	Group meeting	Face-to-face	Telephone	Face-to-face
Time line	1 month (following baseline assessment)	2 months	3 months	4 months	5 months	6 months
Duration	30 min	15 min	90 min	30 min	15 min	30 min
Who delivers	Dietician and/or physiotherapist	Dietician and/or physiotherapist	Psychologist, dietician and physiotherapist	Dietician and/or physiotherapist	Dietician and/or physiotherapist	Dietician and/or physiotherapist
Social support	-	-	Invited friend/partner/family member	-	-	-
Motivational approaches	1/2 week diet/activity diaries assessment	Identify perceived diet/activity challenges	Coping and provide opportunities to learn from each other	1/2 week diet/activity diaries assessment	Identify perceived diet/activity challenges	1/2 week diet/activity diaries assessment

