The primary outcome measure will be assessed at the end of the 6-month intervention, by measuring the body weight. We expect a body weight reduction ≥5 % of the baseline body weight in all the intervention arms. The secondary outcome measures will be assessed through the intervention during the follow-up visits: (a) we expect weight control over the study period, measuring the body weight at each follow-up visit; (b) we expect an increase in physical activity levels and reduction in physical inactivity from baseline measured by the pedometer-like devices and from the IPAQ questionnaire. The physical activity target for improving general health is 30 minutes of moderate-to-vigorous intensity every day (equivalent to 10 MET-hours per week) and reducing inactivity; (c) we expect a change in dietary intake and an increased adherence to healthy diet from baseline using the FFQ; (d) we will evaluate the effect of the intervention on long-term breast cancer recurrence; (e) we expect an improvement in quality of life and in health status from baseline using the FACT-B and STAI; (f) we will evaluate the effect of intervention on the blood lipid profile. We expect an increase in HDL cholesterol and a decrease in LDL cholesterol, triglycerides and total cholesterol; (g) we will evaluate the effect of intervention on some biomarkers: estradiol, CRP, insulin, and glucose. Statistical analyses will only be carried out after the end of the trial, with no interim analysis planned.

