### Statistical methods

All continuous variables (anthropometric, biomedical, nutritional and psychological measurements) at baseline and at the primary time point (6-month) will be checked for normality and transformed as needed. The Student *t* test, analysis of covariance (ANCOVA) and multiple linear regression models will be used to assess changes in means before and after the intervention. All tests will be two-sided and *P* values <0.05 will be considered statistically significant.

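### The 6-month food frequency questionnaire asks about the previous year, so half of its window precedes randomisation and the between-arm diet difference at 6 months is diluted

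*Protocol article*

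**What the plan says.** Measures, in the protocol article, fixes the instrument and its timing: "Dietary intake will be measured at baseline, 6 and 24 months using the validated and self-administered food frequency questionnaire (FFQ"). It then gives the recall period: "It records daily intake of foods and nutrients over the previous year".

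Statistical considerations, item (c), makes this questionnaire the tool for a secondary outcome: "we expect a change in dietary intake and an increased adherence to healthy diet from baseline using the FFQ". Statistical methods brings nutritional variables into the 6-month analysis; continuous measurements "at baseline and at the primary time point (6-month) will be checked for normality and transformed as needed".

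Study design sets the length of treatment: "Randomized patients will receive a 6-month intervention and will be followed for further 18 months". The Intervention section places baseline before allocation: "Baseline assessment will be made for all participating women, prior to randomization in one of the four intervention arms". In Table 2 the first contact, at which personal goals are set, is timed at "1 month (following baseline assessment").

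Table 1 also lists 24-h recalls and/or food diaries at baseline and 6 months, under a dietary-target row. Its footnote gives them a different job: "24 hr recalls and/or food diary and the pedometer-like device will be used during the intervention to monitor individualized goals". No section shortens the FFQ reference period at 6 months or mentions the overlap.

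**The concern.** A one-year recall is being used to detect the effect of a six-month programme. The months before randomisation have the same expected diet in every arm, so including them adds nothing to the contrast and shrinks it.

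Two readings of the results are at risk:

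- A small or null diet difference at 6 months could be taken to mean that the dietary arms did not change what they ate, when part of the shortfall comes from the recall window.
- The 6-month and 24-month differences cannot be set side by side, because only the first is diluted. Maintenance could look like further improvement, and relapse could look like maintenance.

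Physical activity does not share the problem. The International Physical Activity Questionnaire, described in the same section, asks about the previous 7 days.

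**Working it through.** The article gives no effect size, standard deviation or power for diet, so there is no stated figure to reproduce. The check is arithmetic on the recall windows.

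**Inputs.** Recall window 12 months (Measures). FFQ at months 0, 6 and 24 (Measures, Table 1). Baseline before randomisation, taken as month 0 (Intervention). First contact at month 1 (Table 2).

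**Step 1: windows.** Baseline FFQ: months -12 to 0. 6-month FFQ: months -6 to +6. 24-month FFQ: months 12 to 24. The share before randomisation at visit month v is max(0, 12 - v)/12:

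- v = 6: 6/12 = 50%. These six months are also the second half of the baseline window.
- v = 24: 0/12 = 0%.

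**Step 2: share of a change recorded at month 6, if women report a true, equally weighted 12-month average (assumption).** Let g(t) be the fraction of the full change reached by month t, with g = 0 before randomisation. The retained share is the area under g from month 0 to 6, divided by 12. The last column divides the same area by 6, as a window starting at randomisation would.

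| Course of change (assumed) | Area | Previous-year window | Window since randomisation |
|---|---|---|---|
| Immediate, sustained | 6 | 6/12 = 50% | 6/6 = 100% |
| Full change from month 1 | 5 | 5/12 = 42% | 5/6 = 83% |
| Linear over months 0-3, then full | 1.5 + 3 = 4.5 | 4.5/12 = 38% | 4.5/6 = 75% |
| Linear over months 0-6 | 3 | 3/12 = 25% | 3/6 = 50% |
| Linear over months 1-6 | 2.5 | 2.5/12 = 21% | 2.5/6 = 42% |

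In the gradual cases, part of the shortfall arises because the full change is reached only at month 6. Under equal weighting, the shorter window doubles the retained share in every row.

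**Step 3: recall that favours recent months (assumption).** Weight a month lying s months before the visit by exp(-s/T). For an immediate change the retained share is (1 - exp(-6/T))/(1 - exp(-12/T)) = 1/(1 + exp(-6/T)):

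- T = 12 months: 1/(1 + 0.607) = 62%
- T = 6 months: 1/(1 + 0.368) = 73%
- T = 3 months: 1/(1 + 0.135) = 88%

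**Step 4: comparability of visits, under equal weighting.** An immediate difference of 1 unit held to month 24 is recorded as 0.5 at 6 months and 1.0 at 24 months, an apparent doubling. A difference of 1 unit over months 0-6 that has fallen to 0.5 throughout months 12-24 is recorded as 0.5 at both visits, which looks like maintenance.

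**The case against.** The strongest reply concerns size. Nothing in the article says how women weight recent months, and a woman six months into a diet programme may well describe what she eats now. This stands: the overlap is fixed by the article's own figures, but the amount of dilution is not. A reader might infer that the measured change is simply halved. That holds only for an immediate change and equally weighted recall. The 5/12 figure is also soft, because the Intervention section calculates energy requirement at baseline and change need not wait for the first contact.

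A reader might also infer that four times as many women would be needed. The article does not support this. It states no power for diet, and the sample size rests on weight alone. The inverse-square rule also needs an unchanged standard deviation, whereas averaging over a half-untreated year would shrink the spread of true diet changes along with their mean. A further tempting reading is that the trial would wrongly deny that weight loss came through diet; no mediation analysis is planned.

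On timing, item (c) names no visit, and the Intervention section places secondary assessments at 12 and 24 months. However, Table 1 schedules the FFQ at 6 months, and Statistical methods covers nutritional variables at that time point. A 6-month diet analysis is therefore part of the plan, though not the only one.

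Short-window diet data are planned too, and the Serious adverse events section describes recalls or diaries for all participants. This softens the consequence, but their stated roles are monitoring and safety, and item (c) names only the FFQ.

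Lastly, the article condenses a fuller protocol that might contain visit-specific instructions. The recall period, visits and outcome role are nevertheless stated here without exception. Once the answers are collected, no analysis plan can recover the diet of months 0 to 6 from them.

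**Conclusion.** The point holds as a weakness in how one secondary outcome is measured at one visit. Half of the 6-month FFQ window precedes randomisation and overlaps the baseline window. The 6-month between-arm diet difference is therefore biased towards zero and cannot be compared directly with the 24-month one.

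The share of a true change retained at 6 months is about 50% if the change is immediate and women report a true 12-month average, 21-42% if it is delayed or gradual under the same averaging, and 62-88% if it is immediate and recall favours recent months (time constants of 12 to 3 months). These are scenarios, not documented values.

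The consequence is lost sensitivity, not a spurious effect. The 24-month FFQ and the primary weight outcome are unaffected. The change should be made, but the trial's main conclusion does not depend on it.

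**What to change.** **Preferred.** At the 6-month visit, give the FFQ in all four arms with the reference period set to the time since randomisation, leaving the baseline and 24-month forms as they are. Base inference on the between-arm comparison adjusted for the baseline FFQ; analysis of covariance is already among the named methods.

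**Otherwise.** Make the 24-h recalls or food diaries listed in Table 1 at baseline and 6 months the 6-month dietary outcome, and use the FFQ only for baseline to 24 months. This requires choosing between recall and diary, which Table 1 leaves open, and collecting the chosen one on the same schedule in all four arms, including the less intensive arm.

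**Cost.** The preferred change alters the instruction on one form but departs from the validated one-year period. Change within a woman would then mix diet with season and reference period. That applies equally across arms, which is why the between-arm comparison should carry the inference. Data collection, storage and security sends FFQ data through a dedicated conversion database, so check first that it accepts a shorter period. Because recruitment is already under way, record which form version each woman completed.

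Whichever route is taken, state in the report that FFQ changes at 6 and 24 months refer to different windows.
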